### Profile person-centred care

Based on scientific evidence, an ethical framework, and clinical practice, the University of Gothenburg Centre for Person-Centred Care (GPCC) has developed a model for person-centred care, constituting three routines: i) Initiating a partnership, ii) Establishing an agreement between patient and healthcare provider, and iii) Safeguarding the partnership through documentation [32,33], Figure 3. To support health care units implementing the person-centred care model, GPCC has developed an online training programme, ‘MedMänniska’ [Mutual Meetings] that supports professionals´ learning and training and equipping them with tools to implement person-centred care in their respective health care context [34]. This training programme will be implemented in the midwifery education programme and consists of ten lessons focusing the three routines in person-centred care. Its didactive method includes theory, individual reflections, common discussions, and exercises. Mutual Meetings, to our knowledge, have not been reported to be used in any low-income settings.

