### Profile simulation-based learning

Theoretical knowledge, simulation-based learning, and practical clinical training will be integrated in the midwifery education programme at both campus and clinical practice sites. As part of this simulation-based education at clinical practice, selected gynecologists and midwives will be trained to become facilitators. This study concerns implementation of three selected simulation-based learning courses: i) Essential Care for Labor and Birth (ECLB), ii) Vacuum Assisted Birth (VAB) and iii) Bleeding After Birth Complete (BABC).

The implementation strategies include the following steps:
Facilitators (*n* = 12) from each clinical site (*n* = 5) will be trained in the courses ELCB, VAB, and BABC during a 4-day facilitator training and will after completion of the courses train their colleagues at their respective maternity units (*n* = 50). The training will use the low-dose, high-frequency approach. In total, about 50 healthcare providers will be capacitated to function as preceptors for midwife students, using the ELCB, VAB, and BABC courses.The maternity care units (*n* = 5) will each receive necessary pedagogic tools related to the ECLB-, VAB-, and BABC courses including posters, flipcharts, and facilitator guides for each course as well as birth simulator mannequins and vacuum extractors.The clinical preceptors will subsequently train the midwifery students, using the low-dose, high-frequency approach aiming for weekly trainings in clinical setting through simulation-based training by utilizing the education material and mannequins provided in the ELCB, VAB and BABC courses. The person-centred care approach will be included in the simulation-based learning scenarios.

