To further investigate the effect of the intervention’s impact on the quality of care, particularly the influence on maternal and neonatal outcomes at the five clinical practice sites, we will collect quantitative data from the birth register, Table 1. All births for the years 2022 and 2024 will be included.

**Table 1. t0001:** Variables collected in birthregisters.

Mode of birth: Jan–Dec 2022–Jan–Dec 2024
Vaginal spontaneous birth
Caesarian birth emergency
Planned caesarian birth
Maternal mortality
Neonatal mortality
Obstetrical complications
Still births Fresh
Postpartum Hemorrhage >500 ml
Vacuum assisted birth

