## Impact of the research

At policy level: Through the results of this research, we hope for successful implementation of person-centred care in midwifery education and clinical practice in low-income settings. This could pave the way for policy recommendations promoting its widespread adoption across healthcare professions in the DRC and other similar contexts.At education level: We anticipate that the validated training programme ‘Mutual Meetings’ serves as a foundation and could be extended beyond midwifery to enhance healthcare education [20]. The new knowledge generated provides an opportunity for governments, researchers, and policymakers in the DRC and elsewhere to integrate person-centred care and simulation-based learning into midwifery education programmes, contributing to improved quality of care.In quality of care: If the intervention has positive effects on maternal and newborn health outcomes, such as increased proportion of vaginal birth and reduced morbidity and mortality and thus improving women’s childbirth experiences, we can through this intervention prove that equipping midwives with competence in person-centred care and simulation-based learning offers a strategic approach to improving maternal and newborn health.

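### Register-recorded haemorrhage >500 ml, and to a lesser degree obstetrical complications, are compared before and after as effect outcomes although the bleeding course can change how often they are recognised and recorded

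*Protocol article*

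**What the plan says.** Data collection gives the purpose of the register data: "To further investigate the effect of the intervention’s impact on the quality of care, particularly the influence on maternal and neonatal outcomes". The source is stated as "we will collect quantitative data from the birth register, Table 1", and the periods as "All births for the years 2022 and 2024 will be included". Table 1 includes "Postpartum Hemorrhage >500 ml" and "Obstetrical complications".

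Data analysis compares the maternal and neonatal outcomes between the two periods, with Fisher's exact test for dichotomous variables, two-sided at the 5% level. No concurrent comparison group is described.

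Profile simulation-based learning names three courses, of which one is "Bleeding After Birth Complete (BABC"). Facilitators from the clinical sites take the courses and then train colleagues in their own maternity units. About 50 providers in all are to act as preceptors, and weekly training of students is the aim. Monitoring visits adds weekly follow-up of each site by a coordinator.

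The Hypothesis section expects better maternal and neonatal outcomes. Impact of the research describes positive effects "such as increased proportion of vaginal birth and reduced morbidity and mortality" and says that, if they are seen, the study can prove the value of the approach.

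**The concern.** A 500 ml threshold depends on how blood loss is assessed and whether the result is written down. A general complications entry depends on what staff recognise as a complication. A course on bleeding after birth is directed at the people in the units where those judgements are made. The recorded rate can therefore move between 2022 and 2024 for two reasons: a change in true morbidity, or a change in the share of true cases that reach the register.

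A before-and-after comparison of raw rates gives only the product of the two. A significance test does not help, because it tests whether the recorded rates differ and not why. If detection improves, the most likely errors run against the authors' own hypothesis: a real reduction is diluted or hidden, or an unchanged rate looks like harm.

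**Working it through.** **No figure to reproduce.** The article states no birth count, haemorrhage rate, target effect or power. Every rate, recording share and birth count below is an assumption. The article supplies only the outcomes, the two periods, the test and the 5% two-sided level. I also take 2024 as the exposed year, as the comparison implies; the text gives no training dates.

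**Model.** Let p be the true rate and s the share of true cases recorded, with no false positives.

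- Recorded rate = p × s
- Recorded RR = true RR × (s2024 / s2022)

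**Recorded RR**

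| Recording share, 2022 to 2024 | Ratio | True RR 1.00 | True RR 0.80 |
|---|---|---|---|
| 50% to 50% | 1.00 | 1.00 | 0.80 |
| 70% to 80% | 1.14 | 1.14 | 0.91 |
| 50% to 60% | 1.20 | 1.20 | 0.96 |
| 50% to 62.5% | 1.25 | 1.25 | 1.00 |
| 50% to 75% | 1.50 | 1.50 | 1.20 |

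A benefit is fully hidden when s2024 / s2022 = 1 / true RR. That ratio is 1.11 for a true RR of 0.90, 1.25 for 0.80 and 1.43 for 0.70.

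**Test results with no true effect, true rate 6%** (pooled two-proportion z; Fisher's exact test would be slightly more conservative)

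- 50% to 75%: 0.06 × 0.50 = 3.0% and 0.06 × 0.75 = 4.5%. At 2,500 births per year, SE = √(0.0375 × 0.9625 × 2/2,500) = 0.00537 and z = 0.015/0.00537 = 2.79, p = 0.005. At 5,000 births, z = 3.95, p = 0.00008.
- 70% to 80%: 0.06 × 0.70 = 4.2% and 0.06 × 0.80 = 4.8%. At 5,000 births, SE = √(0.045 × 0.955 × 2/5,000) = 0.00415 and z = 0.006/0.00415 = 1.45, not significant.

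**Chance of a significant false increase, no true effect** (normal approximation). At a 6% true rate and 5,000 births per year it is 0.30 for 70% to 80%, 0.39 for 50% to 60% and 0.90 for 50% to 70%. For 50% to 70%, it runs from 0.30 to above 0.99 across 2,000 to 10,000 births and true rates of 3% to 10%.

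**Chance of showing a real 20% reduction** at 6% and 5,000 births: 0.46 if recording stays at 50%, and about 0.05 if it rises from 50% to 60%.

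**The case against.** The best defence is that the mechanism is inferred. The article does not say that training alters recognition or recording, who assesses blood loss, who fills in the register, or what share of births trained staff attend. All of this is right. The point is that recording can change, not that it will.

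Some stronger readings are tempting, and the text does not carry them:

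- **Documentation routine.** A reader might link register completeness to the person-centred routine "Safeguarding the partnership through documentation". That routine documents the partnership between patient and provider. It says nothing about blood loss or birth registers. The bleeding course is the anchor, and it bears directly on haemorrhage and only indirectly on complications in general.
- **Success rule.** The sentence in Impact of the research is conditional and does not name haemorrhage. Data analysis sets two-sided comparisons and no success criterion.
- **Confirmatory status.** The Abstract and Research design call the work exploratory, and no primary outcome is named. This softens the point. It does not remove it, because the article also states an effect hypothesis, tests at 5% and speaks of proof.
- **Missing definitions.** How blood loss was measured and how complications are defined may stand in a fuller document. Their absence from an article is not the finding.

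The size is also open. A modest shift such as 70% to 80% dilutes a benefit and need not produce a significant false increase. The direction depends on the model as well: if the 2022 register overcalled haemorrhage, better assessment could lower the recorded rate and imitate benefit.

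What remains is the structure fixed in the text: same units, a bleeding course, register outcomes and an uncontrolled comparison.

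**Conclusion.** The concern holds as a limit on interpretation. A change in register-recorded haemorrhage >500 ml between 2022 and 2024 cannot by itself be read as an effect of the intervention in either direction. The same applies, with weaker support, to the complications item.

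The size is unknown. If detection improves and false positives are negligible, the recorded RR is too high by exactly the ratio of recording shares. A 1.25-fold rise is enough to hide a true 20% reduction completely. Whether a false increase would reach significance depends on assumed rates, shares and birth counts. The documents do not support a claim that the study will show false harm.

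**What to change.** 1. Label haemorrhage >500 ml and obstetrical complications as descriptive and detection-sensitive. State before the 2024 data are analysed that a rise is not read as harm and a fall is not by itself read as proof of benefit.
2. Base effect statements mainly on Table 1 outcomes less exposed to detection: maternal death, fresh stillbirth combined with neonatal death, and mode of birth. None is immune. Classing a stillbirth as fresh is a judgement. Mode of birth is a clinical decision that the vacuum course targets, so it should be presented as a reliably recorded practice outcome and not as a measure of morbidity.
3. From the same extract, report completeness of the two fields by site and month for both years. This shows changes in recording practice but not missed cases, so it informs the reading without correcting the estimate.
4. Add a sensitivity analysis that divides the observed RR and its confidence limits by a range of recording ratios, for example 1.0 to 1.5 with some values below 1, and report the ratio at which the conclusion changes.

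**Cost.** This needs a few sentences, one table and a simple recalculation, with no new data. The price is a weaker claim on haemorrhage, the outcome the bleeding course targets. Deaths are also sparse. If the national rate quoted in the Background (547 per 100,000 live births) applied, 5,000 births would give about 0.00547 × 5,000 = 27 maternal deaths a year, so mortality comparisons will be imprecise and should be reported with their intervals.

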### Data analysis

Analysis of qualitative data from focus group interviews will be based on transcribed interviews, applying deductive qualitative content analysis principles [36]. The process evaluation framework will guide the analysis, emphasizing key components such as Implementation, Mechanisms of Impact, and Outcomes [31].

The maternal and neonatal outcomes will be compared between the two time periods, where Fisher’s exact test will be used for dichotomous variables and the Chi-square test for non-ordered categorical variables. The mean differences with 95% confidence intervals and p-values will be the main results in the comparative analysis. All the tests will be two-sided and conducted at the 5% significance level.

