### Setting

The Evangelical University in Africa is situated in Bukavu in eastern DRC. In October 2022, a 90 credits midwife education programme started at the faculty of Medicine and Community Health for nurses, having a 3-year education on university level. The programme is at the bachelor level and adheres to the national curriculum. However, it is further innovatively designed with a profile of person-centred care and the integrated use of simulation-based learning pedagogy and materials. The clinical practice sites are situated at five hospitals located in the South and North Kivu provinces in eastern DRC.

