### Intervention

The intervention involves integrating two profiles into a midwifery education programme aligned with the national curriculum, namely person-centred care, and simulation-based learning. The strategy used to implement and integrate the two profiles into clinical practice is training facilitators from each clinical site to further ensure effective and sustained implementation.

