### Monitoring visits

A local project coordinator will do weekly follow-ups and visits with each of the five clinical practice sites to ensure effective implementation of the individual implementation plans. The objective of the monitoring visits is to support and enhance the implementation of person-centred care and simulation-based learning at the clinical sites by ensuring management approval, providing continuous support to facilitators, and maintaining effective communication throughout the project. The local project coordinator will work as an external facilitator while the trained facilitators based at each clinical practice site will work as internal facilitators. Internal facilitators are identified as facilitators working in the implementation site [18] and the external facilitator refers to facilitation that comes from a change agency outside of the implementation site [35].

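### The 2022 versus 2024 birth-register tests have no place for hospital, so shifts in site volume can move the result, and unequal change between hospitals would make p-values for common outcomes too small

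*Protocol article*

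**What the plan says.** The quantitative analysis is set out in the second paragraph of Data analysis in the protocol article. It opens: "The maternal and neonatal outcomes will be compared between the two time periods, where Fisher’s exact test will be used for dichotomous variables". For other variables it names "the Chi-square test for non-ordered categorical variables". It continues: "The mean differences with 95% confidence intervals and p-values will be the main results in the comparative analysis". It closes: "All the tests will be two-sided and conducted at the 5% significance level".

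The data are all births in 2022 and 2024 in the registers of the practice sites (Data collection, Table 1). The stated interest is "particularly the influence on maternal and neonatal outcomes at the five clinical practice sites". Setting describes these sites: "The clinical practice sites are situated at five hospitals located in the South and North Kivu provinces in eastern DRC".

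The intervention works through the hospitals. Intervention gives the strategy as "training facilitators from each clinical site to further ensure effective and sustained implementation", and Monitoring visits has a coordinator following up "each of the five clinical practice sites to ensure effective implementation of the individual implementation plans". Under Profile simulation-based learning, each of the five maternity units receives its own teaching materials.

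The article does not name site as a stratum, covariate or cluster in the comparison.

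**The concern.** A Fisher or Chi-square table of period against outcome treats all births in a year as independent, with one common probability. Births here are grouped in five hospitals that receive the intervention as units, each under its own plan. Two things can go wrong.

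- **Site mix.** No hospital's share of births is fixed by design. If a hospital with a high caesarean rate takes a larger share in 2024, the merged rate rises although no hospital has changed.
- **Error variance.** If hospitals move differently between the two years, for whatever reason, that variation belongs in the standard error. The named tests leave it out.

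The stake is how the result is read. The article hypothesises improved maternal and neonatal outcomes, and Impact of the research says that positive effects, including a higher proportion of vaginal births, would prove the value of the approach. Mode of birth is a common outcome, where both problems are largest.

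**Working it through.** The article gives no births per site, site rates, sample size or power, so there is no figure of its own to reproduce. The inputs below are assumptions unless marked.

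**1. Site mix.** Assume one hospital with 50% caesareans whose share of births goes from 20% to 30%, while all others stay at 25%.

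- 2022: 0.20 × 0.50 + 0.80 × 0.25 = 0.300
- 2024: 0.30 × 0.50 + 0.70 × 0.25 = 0.325
- Mean rate 0.3125, so z = 0.025 / √(0.3125 × 0.6875 × 2/N)
- N = 5,000 births per year: z = 2.70, p = 0.007
- N = 10,000 births per year: z = 3.81, p = 0.0001

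The change inside every hospital is zero.

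A second set of assumptions uses fixed site rates of 15, 20, 25, 35 and 45%, 5,000 births per year, and equal shares of 20% in 2022. Again no hospital changes:

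| 2024 shares (%) | Merged difference | Fisher p | Mantel-Haenszel difference |
|---|---|---|---|
| 18/19/20/21/22 | +0.8 points | 0.41 | 0.000 |
| 15/17.5/20/22.5/25 | +1.9 points (95% CI 0.1 to 3.7) | 0.040 | 0.000 |
| 10/15/20/25/30 | +3.8 points (95% CI 2.0 to 5.6) | 0.00004 | 0.000 |

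**2. Error variance.** Let p be the prevalence, m the births per site per year (equal across sites), and τ the SD across sites of the 2022-to-2024 change on the logit scale, with average change zero. On the probability scale the change has SD of about τp(1−p).

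- Binomial variance of the merged difference: 2p(1−p)/(5m)
- Added variance from unequal site change: τ²p²(1−p)²/5
- Variance inflation: D = 1 + mτ²p(1−p)/2
- True two-sided error: 2 × [1 − Φ(1.96/√D)]

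With p = 0.30 and τ = 0.1, D = 1 + 0.00105m:

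| m | D | True type I error | Interval should be wider by |
|---|---|---|---|
| 500 | 1.525 | 11% | × 1.23 |
| 1,000 | 2.05 | 17% | × 1.43 |
| 2,000 | 3.10 | 27% | × 1.76 |
| 3,000 | 4.15 | 34% | × 2.04 |

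Simulation of a merged z-test gave 10, 17, 26 and 32%. With τ = 0.2 the formula gives 27% at m = 500 and 60% at m = 3,000. With τ = 0, D = 1 and the error is 5%. Simulating hospitals with fixed, different rates and an unchanged mix gave 4.3%, so stable differences between hospitals do not inflate the error.

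**3. Rare outcomes.** The national rates in the article's Background (547 maternal deaths per 100,000 and 28 newborn deaths per 1,000 live births) serve as assumed stand-ins for site rates. With τ = 0.1 and m from 500 to 3,000:

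- Maternal mortality: D = 1.01 to 1.08, error about 5% to 6%. Simulating Fisher's test itself gave 2.9% to 4.3%, because the exact test is conservative with few events.
- Neonatal mortality: D = 1.07 to 1.41, error about 6% to 10%. Simulated Fisher gave 5.5% to 10.4%.

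With τ = 0.2 the formula gives about 6% to 9% for maternal and 8% to 23% for neonatal mortality.

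**4. Which repair suits rare outcomes.** At 500 births per site and 547 per 100,000, the chance of no death in a site-year is (1 − 0.00547)^500 = 0.064. Over ten site-years the chance of at least one zero is 1 − (1 − 0.064)^10, about 49%. A site-specific log odds ratio would then be undefined without an ad hoc correction.

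**The case against.** **Pooling is not stated.** The article says only that outcomes are compared between the periods, and a reader could imagine one table per site. This limits the certainty of the point. The natural reading of a two-period test with one main result is still a single table over all sites. For mode of birth, if treated as one variable, that table would be larger than 2×2.

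**Detail may sit in an unseen analysis plan.** Site adjustment and sensitivity analyses often do, and their absence from an article is no fault. The point here is the test that the article does name.

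**The harms are conditional.** A reader might infer that the 5% level and 95% intervals simply fail. The documents do not support that. Mix bias needs both shifting shares and unequal baseline rates, and a small shift gave p = 0.41. Inflation needs hospitals to change differently. The article gives none of these quantities, though individual site plans and a two-year gap make unequal change plausible.

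**The large figures do not carry over to all of Table 1.** This stands. They apply to common outcomes. For maternal mortality the inflation is small, and Fisher's test may stay below 5%.

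**The study is exploratory and uncontrolled.** This also stands in part: the lack of a concurrent control limits a causal claim more than the handling of site does. But the article sets a significance level and an outcome hypothesis, and handling site properly costs little.

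**Conclusion.** The point holds in conditional form. The named tests, read as written, give a valid comparison only if site mix is stable or irrelevant and all five hospitals drift alike. The article gives no basis for assuming either.

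Under the stated assumptions, a shift in site volume alone can produce a nominally significant difference of about 2 to 4 percentage points. Unequal site change with SD 0.1 on the logit scale raises the error for a 30% outcome to between 11% and 34% over 500 to 3,000 births per site per year. These sizes illustrate the problem; they do not predict this study's data.

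Two stronger readings should not be drawn: that every outcome in Table 1 is affected to this degree, and that a site-stratified analysis would isolate the effect of the intervention. A within-site difference between 2022 and 2024 still contains secular trend and case-mix change.

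**What to change.** 1. Keep hospital (and month of birth, if the regression in point 3 is used) as a column in the register extract.
2. For every outcome, replace the merged comparison with a site-stratified (Mantel-Haenszel) risk difference and 95% confidence interval.
3. For common outcomes such as mode of birth, base the test and interval on the five within-site differences with a t reference on 4 degrees of freedom, or on a regression with site fixed effects and overdispersion across site-months. Choose one, and its weighting, before the 2024 data are analysed.
4. For rare outcomes such as maternal death, use a stratified exact or Mantel-Haenszel method. Do not combine site-specific log odds ratios.
5. Show the five site results beside the combined one for every outcome.
6. State that the comparison has no concurrent control, so trend and case-mix change remain in the estimate.

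The cost is a few sentences of analysis text and the extra column or columns. Intervals become wider: with five differences the critical value is 2.78 instead of 1.96, a factor of 1.42 before any added variance.
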